# A randomized phase II study of S-1 monotherapy versus cisplatin with vinorelbine for completely resected stage II/IIIA non-small cell lung cancer: rationale and study protocol design for the LOGIK1702 study

**DOI:** 10.1186/s12885-021-07945-y

**Published:** 2021-03-08

**Keywords:** Adjuvant chemotherapy, S-1, Cisplatin, Feasibility study, Quality of life non-small cell lung cancer

## Abstract

**Background:**

The current standard postoperative treatment for stage II-IIIA non-small cell lung cancer (NSCLC) is a regimen of platinum doublet adjuvant chemotherapy. These regimens, which are the same as for solid NSCLC tumors, often cause severe adverse reactions in the treated patients. Therefore, an effective treatment regimen with fewer side effects is needed.

**Methods/design:**

The purpose of this study is to evaluate the effectiveness and safety of S-1 monotherapy (80 mg/m^2^ orally administrated twice daily, at day 1–14, 16 cycles) and cisplatin with vinorelbine combination therapy (cisplatin 80 mg/m^2^ at day 1,vinorelbine 25 mg/m^2^ at day 1, 8, 4 cycles) in patients with II/IIIA stage non-small-cell lung cancer who underwent a total resection. In addition, we will also evaluate the level of treatment side effects by assessing quality of life (QOL), work productivity and activity performance. The primary endpoint is a 2-year relapse free survival (RFS) and the second primary endpoints are 2-year overall survival (OS), rate of treatment completion, safety, work productivity and activity, and quality of adjusted life years (QALY). At the same time, we aim to obtain precise information required to perform future phase 3 randomized controlled trials. The study is designed to estimate the primary endpoint with accuracy determined as the width of its 95% confidence interval to be less than 20%. Recruitment started in May 2017 and is ongoing.

**Discussion:**

This study has been conceived to establish a superior regimen for completely resected NSCLC based on efficacy, safety and QOL.

**Trial registration:**

Registry number: UMIN000027435. Registered May 22, 2017.

## Background

Lung cancer remains the leading cause of cancer-related deaths worldwide. In order to prevent lung cancer recurrence, adjuvant chemotherapy in post-operative patients with stage IB-IIIA non-small cell lung cancer (NSCLC) has been established as the standard treatment [1–3]. The standard regimen for adjuvant chemotherapy is intravenous administration of a platinum doublet [3]. However, the representative regimen of cisplatin (CDDP) with vinorelbine (VNR) causes grade three or four adverse reactions including severe leukopenia, neutropenia, anemia, aspartate aminotransferase (AST) elevation, nausea, vomiting, constipation, asthenia, injection site reaction, and prolonged peripheral neuropathy in more than 70% of patients. Renal dysfunction often occurs and sometimes remains lifelong. Given the severe adverse reactions to this standard adjuvant chemotherapy and the fact that there are few remnant malignant cells in the postoperative patients, milder treatment options have been considered.

A recent study of the 5-year survival in a randomized phase III study of cisplatin with pemetrexed versus cisplatin with vinorelbine for completely resected stage II-IIIA non-squamous NSCLC (the JIPANG study) was reported (ASCO 2019 8501). The JIPANG study failed to show the superiority of pemetrexed plus cisplatin over vinorelbine plus cisplatin and the cost of pemetrexed is high. However, the regimen will be considered as an option for adjuvant chemotherapy for stage II-IIIA non-squamous NSCLC since the effect is comparable and the patients treated with cisplatin and pemetrexed had a higher completion rate with low adverse reactions compared to the patients treated with cisplatin and vinorelbine. Another recent approach is the use of immune checkpoint inhibitors (ICI) for postoperative patients. Several clinical trials of ICI with/without chemotherapy are currently underway in adjuvant setting [4]. The trials are expected to be completed during 2024 or later. Thus the efficacy and the adverse reactions of ICI in adjuvant therapy remain unclear.

S-1 might be another candidate for mild adjuvant chemotherapy for NSCLC. The oral fluoropyrimidine derivative which consists of tegafur and two modulators, 5-chloro-2,4-dihydroxypyridine (CDHP) and potassium oxonate (Oxo), enhances 5-FU efficacy by inhibiting degradation of 5-FU and reduces the GI toxicity caused by 5-FU [5]. The significant effects with low adverse reactions of S-1 monotherapy in an adjuvant treatment have been proven in randomized phase III trials in digestive cancers including gastric, pancreatic and colon adenocarcinomas [6–8]. Accordingly, S-1 based adjuvant chemotherapy has been used as an option of standard treatment in intestinal cancers. Further, S-1 also has efficacy against squamous cell carcinomas including head and neck, oral, esophagus and thymus [9–11], suggesting S-1 is effective on both squamous carcinomas and adenocarcinomas.

Feasibility studies of S-1 based adjuvant chemotherapy for patients with stage IB to IIIA NSCLC have also been conducted [12, 13] . The results indicate that the completion rates of planned one-year treatment courses were comparable to platinum doublet (50–72%) and the grade 3 adverse reactions were very low (4–20%) with no grade 4 adverse reactions. The grade 3/4 neutropenia was extremely low (0–6.7%), compared to the meta-analysis of cisplatin with vinorelbine adjuvant chemotherapy of 80% [14]. The 5-year overall and relapse free survival rates of the S-1 treated postoperative patients with stage IB-IIIA NSCLC were 72.5 and 67.5%, which are obviously better than those of previously reported studies including platinum doublet based adjuvant chemotherapies [12]. The randomized phase II study of adjuvant chemotherapy with S-1 and cisplatin with S-1 revealed that the survival rates of both groups overlap in patients with completely resected stage II–IIIA NSCLC [15], indicating that S-1 monotherapy has the potential for replacing the standard regimen of platinum doublet by virtue of its efficacy and safety.

The low incidence of adverse reaction directly correlates with the quality of life of the treated patients. Because of mild adverse reactions, S-1 can be administrated for outpatients without hospitalization and treated patients can continue daily life and working, which will maintain the social productivity of the treated individuals. The evaluation of quality of life (QOL) and work productivity of postoperative patients shows the advantage of S-1 chemotherapy versus standard platinum doublet adjuvant chemotherapy. Taken together, these findings have enabled us to design the current phase II study to confirm the beneficial effects of S-1 in adjuvant chemotherapy. In this article, we describe the protocol (version 2; January 14, 2020) for this study. The results of this study are expected to provide basic information for raising the precision of performance for a randomized phase III study.

## Methods/design

### Study design and treatment

The present study is a multicenter, phase II, randomized, open-labelled, parallel-group comparison study of the efficacy and safety of S-1 compared with cisplatin plus vinorelbine for adjuvant therapy in patients with NSCLC. The study design is summarized in Fig. 1. Patients are randomized in a 1:1 ratio to the experimental arm (1 year of S-1 administration) or control arm (four cycles of cisplatin with vinorelbine administration), stratified according to sex (female vs. male), age (< 70 years vs. 70 years), pathologic stage (II vs. IIIA) and pathology (squamous cell carcinoma vs. non- squamous cell carcinoma). The primary endpoint is 2-year relapse-free survival (RFS). The secondary endpoints are 2-year overall survival (OS), rate of treatment completion, safety, work productivity and activity, and quality of adjusted life years (QALY). QALY is calculated by the time points of QOL converted from the questionnaire method using Euro QoL 5 dimensions (EQ-5D-5L) [16] and conversion chart. The EQ-5D-5L and work productivity and activity impairment (WPAI) are surveyed by questionnaires for one and a half years from the start of adjuvant chemotherapy (Fig. 2).

**Fig. 1 Fig1:**
[figure not shown]
Study Design of LOGIK1702 Study, A Randomized Phase II Study of S-1 and Cisplatin with Vinorelbine for Completely Resected Stage II/IIIA NSCLC

**Fig. 2 Fig2:**
[figure not shown]
Treatment schedule and outcome measures of arm A (2A) and arm B (2B). ●; Measurements, ▲; Measurable facilities (Once a month), △; optional. *1; Measurements at every 90 (±30) days until 3 years from the start of the treatment. Every 180 (±60) days thereafter.*2; Measurements at every 180 (±60) days until 3 years from the start of the treatment. Every 365 (±90) days thereafter. *3: Measurements at 365 (±60) days and 545(±60) days. *CT Computed tomography, MRI Magnetic resonance imaging, RI Radio isotope, PET Positron emission tomography, WPAI Work productivity and activity impairment questionnaire*

The study is being conducted at 30 institutions in the Lung Cancer Group in Kyusyu (LOGIK) in Japan. The study is registered with the University Hospital Medical Information Network Clinical Trials Registry (www.umin.ac.jp/ctr/) under registration number UMIN000027435. We conduct the study in accordance with the principles of the Declaration of Helsinki. The central ethics committee approved the study.

All eligible patients will be selected and approached on the basis of information derived from the electronic health records of these 30 institutions (academic hospitals) according to the inclusion and exclusion criteria. Participants will be provided with an explanation about the study by their treating physicians, and they will be asked to voluntarily sign an informed consent before participation. If the patient’s consent is obtained, a clinical trial physician will perform the observation/examination based on the description in Fig. 2a and b.

### Eligibility criteria

The main patient inclusion and exclusion criteria are detailed in Table 1.

**Table 1 Tab1:** Main Inclusion and Exclusion Criteria

Inclusion Criteria	
1) Patients providing the written informed consent	
2) Patients with non-small-cell lung cancer histopathologically confirmed	
3) Patients with total resection in pathological clinical stage II - IIIA with more than one lobe excision was carried out	
4) Patients with lymphadenectomy more than ND2a-1 or selective lymphadenectomy	
The selection method of the mediastinal lymph node dissected obeys the following criteria	
●Right upper lobe lung cancer (LC); No.2R,4R	
●Left upper lobe segmentum superius LC; No. 4 L-6	
●Right middle lobe LC;	No.2R,4R,7
●Left upper lobe lingual LC; No.4 L-7	
●Right lower lobe LC; No.7–9	
●Left lower lobe LC; No.7–9	
5) Patients without pre-treatment (radiation, chemotherapy) other than surgical treatment	
6) Patients who passed more than 28 days and less than 56 days after the operation at enrollment	
7) Patient is at least 20 years and less than 75 years of age (at enrollment date).	
8) Patients capable of treatment with oral medicine.	
9) Eastern Cooperative Oncology Group (ECOG) performance status of 0–1	
10) Patients having sufficient bone marrow, liver and renal function tolerable to chemotherapy	
Exclusion Criteria	
1) Patients with active double cancer (synchronous double cancer and asynchronous double cancer within 5 years of progression-free period)	
2) Patients with anamnesis of drug-induced hypersensitivity.	
3) Patients with severe postoperative complications (such as postoperative infection, rapture suture).	
4) Patients with severe complications (such as diarrhoea, intestinal paralysis, ileus, uncontrollable diabetes mellitus, heart failure, kidney failure, liver failure).	
5) Patients with interstitial pattern recognized as apparent interstitial pneumonia in chest CT.	
6) Patients with active infection.	
7) Female patients pregnant or possibly pregnant (will), or nursing.	
8) Patients under treatment with a type of fluorinated pyrimidine antineoplastic.	
9) Patients under treatment of flucytosine.	

### Treatment

Arm A (S-1 monotherapy) is an adjuvant therapy of S-1 for 16 courses (1 year). S-1 80 mg/m^2^ is orally administered twice daily (after breakfast and dinner) from after breakfast at day 1 to after dinner at day 14 (or from after dinner at day1 to after breakfast at day 15) as 21 days of 1 course.

Arm B (Cisplatin with vinorelbine combination therapy) is an adjuvant therapy of cisplatin with vinorelbine for 4 courses. Cisplatin 80 mg/m^2^ at day1 and vinorelbine 25 mg/m^2^ at day 1, 8 are administered as 21 days of 1 course for 4 courses.

### Randomization

After the acquisition of written informed consent and the completion of baseline measurements, the enrolled participants are registered and assigned treatment by the registration center. Participants will be randomly allocated at a ratio of 1:1 (S1 versus Cisplatin with vinorelbine). Randomization will be performed using the block randomization method with randomly varying block length utilizing SAS version 9.4 software (SAS Institute, Cary, NC, USA).

### Statistical design and sample size considerations

This aim of this study is to estimate the 2 year relapse-free survival rate (RFS) for each study arm with sufficient clinical precision. The statistical comparison of the difference in RFS between the two arms is not a primary aim. We designed the sample size to estimate the 2-year-RFS with the accuracy determined to be the width of the 95% confidence interval for the 2 year-RFS to be less than 20%. The 2-year RFS was expected to be 65%. Assuming an estimate at the 95% confidence interval for the 2 year-RFS with the Wilson’s method, 84 patients are necessary for each arm. Estimating around 10% drop outs, we set the total number of patients to be 190. The above sample size was set to assure the statistical power to quantitatively compare the primary point between the arms. The primary goal of this study is to evaluate the clinical significance of the S1 monotherapy by integrating the observed data of the RFSs, QOL and adverse events of the two arms.

Relapse-free survival was defined as the time from the date of the start of treatment to the date of disease progression or death (whichever occurs first) or the date of last contact. Overall survival was defined as the time from the date of the start of treatment to the date of death or last contact. The Kaplan-Meier method will be used to estimate the time-to-event functions of relapse-free survival and overall survival. The log-rank test will be conducted as a reference without setting the significance level.

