## Discussion

Since 2004, cisplatin with vinorelbine has been the preferred treatment for patients who have undergone complete resection of stage II to IIIA NSCLC and the recommended regimen has not been changed in more than 16 years. Because the adverse reactions are severe in the cisplatin with vinorelbine regime, the Lung Cancer Group in Kyusyu (LOGIK) is conducting the LOGIK1702 study in order to compare the efficacy of milder chemotherapy using S-1 compared to the standard regimen of cisplatin with vinorelbine. S-1 chemotherapy has been successfully used for other cancers and is recommended for intestinal adjuvant chemotherapy. In previous studies using cisplatin doublet based adjuvant chemotherapies most of the relapses occurred within 2-years following the operation and the survival curve came to a plateau thereafter [1–3, 15]. In order to estimate the efficacy of the two regimens, the primary endpoint of this study is also configured as 2-year RFS. The other aspect of this study is to evaluate work productivity and activity, and quality of adjusted life years (QALY) by using the questionnaire of the EQ-5D-5L, which was configured as a secondary endpoint. The EQ-5D-5L measures five aspects of the patient’s life: mobility, self-care, usual activities, pain/discomfort and anxiety/depression. Accordingly, the patients’ QALY will be expressed numerically and evaluated objectively. Since better QOL and work productivity are also desired even for postoperative patients, this analysis will evaluate another aspect of the adjuvant chemotherapy in addition to prognosis. Quality of life is important as well as the longevity prognosis. To the best of our knowledge, this is the first prospective study which evaluates the QALY and work productivity in postoperative adjuvant chemotherapy.

The limitation of the present study is that this randomized study is not aimed at evaluating statistical comparison of the difference in prognoses between the two arms. Rather, this study is aimed at providing basic information for improving the performance evaluation of a future randomized phase III study. The LOGIK1702 study will give us new information on the optimal chemotherapy regimen for completely resected NSCLC.

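### The sample size is said to assure power for comparing the arms, but it was derived from per-arm precision alone

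*Protocol article*

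**What the plan says.** All of this is in the protocol article, under Statistical design and sample size considerations, unless noted.

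- The aim is "to estimate the 2 year relapse-free survival rate (RFS) for each study arm with sufficient clinical precision".
- On comparing the arms: "The statistical comparison of the difference in RFS between the two arms is not a primary aim".
- The precision target is "the width of the 95% confidence interval for the 2 year-RFS to be less than 20" percentage points.
- The planning value is a single rate: "The 2-year RFS was expected to be 65" percent. No separate rate per arm is given.
- The result is "with the Wilson’s method, 84 patients are necessary for each arm", raised to 190 in total for roughly 10% dropout.
- The next sentence reads: "The above sample size was set to assure the statistical power to quantitatively compare the primary point between the arms".
- The section ends by making the log-rank test a reference analysis with no significance level fixed.
- The Discussion gives as the study's limitation that "this randomized study is not aimed at evaluating statistical comparison of the difference in prognoses between the two arms".

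**The concern.** Power is a property of a test. It needs a difference (or a margin), a significance level and a sample size. The section gives only the last of these, and that number came from a one-sample interval width. A sentence saying the size was chosen to assure power for the between-arm comparison therefore describes a calculation that is not shown and that the stated number does not reflect.

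What is at stake is how the result is read. Someone who relies on this sentence could treat similar 2-year RFS in the two arms as the outcome of an adequately powered comparison. The interval for the difference would still be wide enough to include a loss of about 14 points on S-1.

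**Working it through.** **Inputs from the article.** 2-year RFS 65%; full width of the 95% Wilson interval below 20 points; 84 per arm; about 10% dropout; 190 in total, so 95 per arm at 1:1 allocation.

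**Inputs assumed here, because the article gives none.** A 10-point difference from 65%, in either direction; significance level two-sided 5%, with one-sided 5% and one-sided 10% as sensitivity. RFS at 2 years is treated as a simple proportion, with every analysed patient followed for 2 years. Results are shown for 84 and 95 analysed per arm.

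**Step 1: reproduce the plan's figure.** Wilson full width = 2z·√[p(1−p)/n + z²/(4n²)] / (1 + z²/n), with p = 0.65 and z = 1.96.

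- n = 83: 0.2011
- n = 84: 3.92 × √(0.002708 + 0.000136) / 1.0457 = 0.1999

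The smallest n that meets the target is 84, as stated. For dropout, 84/0.9 = 93.3, so 94 per arm or 188 in total; the stated 190 agrees with this after rounding. Per-arm precision explains the whole sample size.

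**Step 2: precision of the difference.** With both arms at 65%, half-width = 1.96·√(2 × 0.65 × 0.35 / n).

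- n = 84: 1.96 × 0.0736 = 0.144
- n = 95: 1.96 × 0.0692 = 0.136

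**Step 3: illustrative power.** Normal approximation with pooled variance under the null: power = Φ{[|d| − z·√(2p̄(1−p̄)/n)] / √([p₁(1−p₁) + p₂(1−p₂)]/n)}.

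For 65% vs 75% at n = 84, two-sided 5%: (0.100 − 1.96 × 0.0707)/0.0703 = −0.549, which gives 29.1%.

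| Rates | n per arm | Two-sided 5% | One-sided 5% | One-sided 10% |
|---|---|---|---|---|
| 65% vs 75% | 84 | 29.1% | 40.8% | 55.3% |
| 65% vs 75% | 95 | 32.3% | 44.4% | 58.9% |
| 65% vs 55% | 84 | 26.1% | 37.3% | 51.7% |
| 65% vs 55% | 95 | 28.9% | 40.5% | 55.0% |

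A cross-check on the log-rank scale (Schoenfeld's formula, exponential survival, two-sided 5%) gives 27–33% over the same four cases.

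**Step 4: what the size could detect.** Solving for 80% power at two-sided 5% gives a gain of 18.8 points (84 per arm) or 17.8 points (95 per arm), and a loss of 21.4 or 20.1 points. For a 10-point difference, 80% power would need 329 per arm (65% vs 75%) or 376 per arm (65% vs 55%).

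**The case against.** The best defence is that the article already disclaims a formal comparison. It does so in the opening of the same section, in the status given to the log-rank test, and in the Discussion. The sentence after the disputed one says the arms will be judged by bringing RFS, quality of life and adverse events together. No margin, success criterion or decision rule uses the claimed power. The English is loose in places, so the sentence may have been meant to say only that two reasonably precise estimates can be set side by side. Much of this stands. It limits the seriousness of the point, and it makes a wording slip plausible. It does not rescue the sentence, which speaks of assuring statistical power; if description was meant, the wording still has to change.

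It is also fair that the power figures rest on a difference and significance levels chosen for this check, and that they vary widely with that choice. They are illustrations, not properties that the plan declared.

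A reader might go further and tie the power sentence to the abstract, where the Discussion paragraph says "This study has been conceived to establish a superior regimen for completely resected NSCLC". The article does not support that link. The abstract's sentence goes on to name safety and quality of life alongside efficacy as the basis for judgement, so it is not a claim about testing RFS for superiority. Nothing in the text makes it depend on the power statement.

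**Conclusion.** The point holds as a false statement confined to one sentence. The stated size comes wholly from per-arm precision, and the claim of assured power has no calculation behind it and contradicts the text around it. The finding of contradiction needs no assumption. The ±13.6 to ±14.4 point interval assumes 65% in both arms and complete 2-year follow-up. The power range of 26–59% for a 10-point difference depends also on the assumed difference and the three assumed significance levels. At two-sided 5%, 80% power is reached only for a gain of about 18–19 points or a loss of about 20–21 points.

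A reader might infer that the trial is too small or that its design is faulty. That does not follow: 84 per arm meets the precision target, and the trial does not set out to test a difference. Because the disclaimers are already in the article and no decision rests on the claimed power, this is a correction of wording and not a challenge to the design.

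**What to change.** Delete the power sentence and put in its place: *The sample size provides per-arm precision only; the between-arm comparison is descriptive, and the 95% CI for the difference in 2-year RFS is expected to be about ±14 percentage points.* A short note that this figure assumes 65% in both arms would complete it.

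If the sponsor also wants to give a power figure, it should carry its assumed difference and significance level, since the plan sets neither. The abstract needs no change on this account.

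The cost is one sentence. Sample size, endpoint, analysis and conduct stay as they are. The stated between-arm properties become less favourable, but accurate.

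### The stated aim of finding a superior regimen, and the integrated two-arm evaluation, go beyond a design sized only for per-arm precision; the RFS difference and its confidence interval should be reported first

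*Protocol article*

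**What the plan says.** Three statements in the protocol article promise a judgement between the arms or in favour of S-1:

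- Abstract, Discussion paragraph: "This study has been conceived to establish a superior regimen for completely resected NSCLC based on efficacy, safety and QOL".
- Background, last paragraph: the findings reviewed there allowed the investigators to "design the current phase II study to confirm the beneficial effects of S-1 in adjuvant chemotherapy".
- Statistical design and sample size considerations, on the primary goal: "evaluate the clinical significance of the S1 monotherapy by integrating the observed data of the RFSs, QOL and adverse events of the two arms".

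Other statements withdraw the comparison. The sample-size section says that testing the RFS difference is not a primary aim and that the log-rank test is for reference, with no significance level. The main Discussion lists as a limitation that "this randomized study is not aimed at evaluating statistical comparison of the difference in prognoses between the two arms" and says the trial is meant to inform a future phase III study.

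The size rests on per-arm precision: the target is "the width of the 95% confidence interval for the 2 year-RFS to be less than 20" per cent, "The 2-year RFS was expected to be 65" per cent, and by Wilson's method "84 patients are necessary for each arm". The same section also says this size assures power to compare the arms, but gives no difference, margin, significance level or power.

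On ranking, 2-year RFS is the primary endpoint throughout. Study design and treatment classes overall survival, treatment completion, safety, work productivity and activity, and QALY as secondary.

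**The concern.** An integrated evaluation of two arms is a comparison, whatever it is called. Here it draws on RFS, QOL and adverse events, and the article does not say that the RFS difference and its uncertainty are part of it. One of the three inputs is largely foreseen. The Background gives grade 3 or 4 reactions in more than 70% of patients on cisplatin with vinorelbine, against grade 3 reactions of 4–20% and no grade 4 on S-1. It gives grade 3/4 neutropenia of 80% against 0–6.7%. It also anticipates better QOL with S-1.

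The RFS input is imprecise at this size. Two overlapping per-arm RFS intervals beside a clear toxicity gain could be reported as a superior regimen or as confirmed benefit, although the data could not rule out a material increase in relapse or death. The Background already reasons this way: it takes overlapping survival in an earlier randomized phase II study as a sign that S-1 might replace the platinum doublet. At stake is what the trial can credibly conclude. Its per-arm estimates are not in doubt.

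**Working it through.** **Inputs.** From the sample-size section: 2-year RFS 65% (one value for both arms), full 95% interval width below 0.20, 84 per arm, about 10% dropout, 190 in total. The article gives no between-arm difference or margin, so the true S-1 deficits below are assumptions. RFS at 2 years is treated as a binomial proportion.

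**1. The plan's own figure.** Wilson full width = 2z·√[p(1−p)/n + z²/(4n²)] / (1 + z²/n), with z = 1.96 and p = 0.65.

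- n = 83: 0.2011
- n = 84: 0.1999

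So 84 is the smallest n that meets the target. For dropout, 84/0.9 = 93.3, hence 94 per arm and 188 in total, consistent with the stated 190. The arithmetic is right, and no between-arm quantity enters it.

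**2. Precision of the difference at that size.** Half-width = 1.96·√[2 × 0.65 × 0.35 / n].

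- n = 84: 1.96 × √0.005417 = 0.144, about ±14 points
- n = 95 (no dropout): 0.136

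**3. If S-1 were truly worse.** With control at 65%, S-1 at 65% minus d, and 84 per arm, SE = √[(0.65 × 0.35 + p(1−p))/84], where p is the S-1 rate. The chance that the 95% interval for the difference includes zero is Φ(1.96 − d/SE) − Φ(−1.96 − d/SE).

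For d = 0.10: SE = √[(0.2275 + 0.2475)/84] = 0.0752 and d/SE = 1.33, so the chance is Φ(0.63) − Φ(−3.29) = 0.735.

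| Assumed S-1 rate | Deficit | Interval includes zero |
|---|---|---|
| 60% | 5 points | 90% |
| 55% | 10 points | 74% |
| 50% | 15 points | 49% |
| 45% | 20 points | 24% |

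With 95 per arm, the 10-point figure is 71%. Under exponential survival, 55% against 65% is a hazard ratio of ln 0.55 / ln 0.65 = 1.39.

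**4. Reading the arms separately.** At observed rates of 65% and 45%, the per-arm Wilson intervals are 54.3–74.3% and 34.8–55.6%. They still overlap at a 20-point gap. Placing the two planned intervals side by side is therefore a weak guard against a deficit, and the interval for the difference is the more informative display.

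**The case against.** The strongest reply is that this is an openly declared estimation trial. RFS is the single primary endpoint and alone sizes the study, the other outcomes are classed as secondary, the limit on comparison is admitted, and the stated output is information for phase III. Reading efficacy, toxicity and QOL together is ordinary at this stage, and how to weigh them may be set out in a full protocol or analysis plan not shown here. Also, with a true 10-point deficit, S-1's observed RFS would be below control in 89% of trials (exact binomial, 84 per arm), so the data would usually point the right way.

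Much of this stands, and it rules out several stronger readings that a reader might infer:

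- That RFS has no precedence. It does in the endpoint list. The gap is confined to the integrated evaluation.
- That toxicity may override relapse, or that S-1 will be adopted on toxicity. No such rule is stated.
- That the trial has several primary endpoints, because the abstract says "the second primary endpoints are 2-year overall survival (OS), rate of treatment completion, safety, work productivity and activity, and quality of adjusted life years". The same five outcomes are called secondary in the main text, so this looks like a clerical slip.
- That there is a multiplicity problem. Familywise error presumes significance claims across endpoints. The only test named has no significance level, and no outcome is given power to decide.

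The reply does not remove the conflict between the abstract's aim and the Discussion's limitation. Both are in the published text, as is the integrated evaluation that the article calls its primary goal. The claim of power to compare the arms does not help either, since the size reproduces without any comparative input.

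**Conclusion.** The point holds in a limited form. The article announces a between-arm judgement that its design does not support, and it does not tie that judgement to an estimate of the RFS difference. At 84 per arm and 65% in both arms, that difference is known to about ±14 points. Under an assumed true deficit of 10 points, the 95% interval fails to exclude zero in about 74% of trials (90% at 5 points, 49% at 15). These figures rest on a binomial treatment of 2-year RFS, a normal approximation and deficits the article does not supply. They are not the probability of a favourable verdict on S-1, which cannot be calculated because no rule is stated. They show that a favourable integrated reading is compatible with a material RFS deficit. The sample-size arithmetic for per-arm precision is correct.

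**What to change.** **(a) Abstract (Discussion paragraph) and Background (last paragraph).** Limit the stated conclusion to estimating 2-year RFS in each arm and informing whether and how to run a phase III trial. Make no superiority claim. This matches the main Discussion.

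**(b) Statistical design and sample size considerations.** State that the integrated evaluation first reports the difference in 2-year RFS (S-1 minus cisplatin with vinorelbine) with its 95% confidence interval, expected to be about ±14 points, as an estimate and not a test. QOL/QALY, work productivity and activity, adverse events, treatment completion and overall survival then follow as supportive secondary outcomes. The sentence claiming power to compare the arms should be brought into line with this.

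**(c) Clerical.** In the abstract's Methods/design paragraph, call the further outcomes secondary, as in Study design and treatment.

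A rule that the other outcomes can never offset an RFS deficit is not recommended. Without a margin, it would count against S-1 in about 47% of trials in which the arms are truly equal, and the trade-off itself is debatable.

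**Cost.** Wording only, with no added patients or data. The trial gives up a superiority claim it cannot support and has to show a wide interval.
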